### Study background and flowchart

BaSICS is a large pragmatic critical trial that aims to provide evidence for or against the use of Plasma-Lyte 148 over 0.9% saline and of lower infusion speeds during fluid challenges in critically ill patients. Patients were randomized using a web-based system designed for the trial in a factorial way (blocks of 12 patients), stratified by recruiting site in a 1:1:1:1 ratio to both define a specific fluid group (Plasma-Lyte 148 or 0.9% saline) and slow (333mL/h) or rapid (999mL/h) infusion during a fluid challenge.^(1)^ The details of the inclusion and exclusion criteria have been addressed in the original protocol, together with recommendations for fluid management and safety rules.^(1)^ The planned flowcharts for both interventions are shown in figures 1 and 2, respectively. BaSICS is a large pragmatic trial, and a screening log was not obtained at each site due to the large number of included patients and for local logistics reasons.

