### Sample size calculation, interim analyses and database lock

BaSICS was designed to enroll 11,000 patients. The sample size was calculated estimating 35% mortality within 90 days in the control group (saline and rapid infusion). This was based on data from large Brazilian cohorts, as discussed in the study protocol.^(1)^ The defined sample size allowed for an 89% power to detect a hazard ratio of 0.9 for both interventions assuming no interaction was expected among the study interventions.

Four interim analyses were performed in BaSICS. The first analysis of the first 1,000 patients aimed exclusively at checking the safety of the fluid speed comparison. Three other interim analyses followed at 25% (2,750 patients), 50% (5,500 patients) and 75% of the sample size (8,250 patients). We used very restrictive rules for stopping the trial for efficacy and we shall not adjust p-values for sequential tests (Appendix 1). A database lock will be applied after 90-day follow-up of all patients is obtained and all needed actions to obtain follow-up have been deployed. The baseline features of the included patients will be displayed as in table 1.

**Table 1 t1:** Baseline characteristics of the patients

Characteristics	Plasma Lyte		0.9% Sodium chloride	
	Slow infusion (n = xxx)	Rapid infusion (n = xxx)	Slow infusion (n = xxx)	Rapid infusion (n = xxx)
Age (years)	xx.x ± xx.x	xx.x ± xx.x	xx.x ± xx.x	xx.x ± xx.x
Female sex	xx.x (xx.x)	xx.x (xx.x)	xx.x (xx.x)	xx.x (xx.x)
Weight (kg)	xx.x ± xx.x	xx.x ± xx.x	xx.x ± xx.x	xx.x ± xx.x
Height (m)	xx.x ± xx.x	xx.x ± xx.x	xx.x ± xx.x	xx.x ± xx.x
Source of admission to ICU				
Elective surgery	xx.x (xx.x)	xx.x (xx.x)	xx.x (xx.x)	xx.x (xx.x)
Nonelective surgery	xx.x (xx.x)	xx.x (xx.x)	xx.x (xx.x)	xx.x (xx.x)
Emergency Department	xx.x (xx.x)	xx.x (xx.x)	xx.x (xx.x)	xx.x (xx.x)
Ward	xx.x (xx.x)	xx.x (xx.x)	xx.x (xx.x)	xx.x (xx.x)
Another hospital	xx.x (xx.x)	xx.x (xx.x)	xx.x (xx.x)	xx.x (xx.x)
Another ICU	xx.x (xx.x)	xx.x (xx.x)	xx.x (xx.x)	xx.x (xx.x)
APACHE II	xx.x [xx.x - xx.x]	xx.x (xx.x - xx.x]	xx.x (xx.x - xx.x]	xx.x [xx.x - xx.x]
SOFA	xx.x [xx.x - xx.x]	xx.x [xx.x - xx.x]	xx.x [xx.x - xx.x]	xx.x [xx.x - xx.x]
Mechanical ventilation				
Noninvasive mechanical ventilation > 12 hours	xx.x (xx.x)	xx.x (xx.x)	xx.x (xx.x)	xx.x (xx.x)
Invasive mechanical ventilation	xx.x (xx.x)	xx.x (xx.x)	xx.x (xx.x)	xx.x (xx.x)
Serum creatinine (mg/dL)	xx.x ± xx.x	xx.x ± xx.x	xx.x ± xx.x	xx.x ± xx.x

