### Planned statistical analysis for the primary, secondary and tertiary endpoints

All clinical endpoints shall be presented as similar as possible to those shown in table 2. Categorical variables will be presented as the number and percentage. Continuous variables will be presented as the mean and standard deviation for variables such as age and physiological parameters (blood pressure, sodium and potassium levels). We will favor the presentation of ordinal variables, such as Sequential Organ Failure Assessment (SOFA) score, as the median and interquartile range. An alpha of 5% and 95% confidence intervals will be used unless otherwise stated; similarly, all analyses will be based on the intention-to-treat principle unless otherwise stated. Analyses will be performed with the latest R version available at the end of the patients’ follow-up (most probably version 4.0).

**Table 2 t2:** Outcomes comparing slow versus fast infusion speed and Plasma-Lyte versus 0.9% sodium chloride

Characteristics	Plasma-Lyte	0.9% Sodium chloride	Effect measure	p value*	Slow infusion	Rapid infusion	Effect measure	p value†	p value‡
			(95%CI)		(n = xxx)	(n = xxx)	(95%CI)		
Primary outcome									
90-day mortality	xx.x (xx.x)	xx.x (xx.x)	x.xx (x.xx - x.xx)	x.xx	xx.x (xx.x)	xx.x (xx.x)	x.xx (x.xx - x.xx)	x.xx	x.xx
Secondary outcomes									
Acute renal failure with need for renal replacement therapy within 90 days									
Incidence (per 1000 patient-day)	xx.x	xx.x	x.xx (x.xx - x.xx)	x.xx	xx.x	xx.x	x.xx (x.xx - x.xx)	x.xx	x.xx
At day 1	xx.x (xx.x)	xx.x (xx.x)		-	xx.x (xx.x)	xx.x (xx.x)		-	-
At day 2	xx.x (xx.x)	xx.x (xx.x)		-	xx.x (xx.x)	xx.x (xx.x)		-	-
At day 3	xx.x (xx.x)	xx.x (xx.x)		-	xx.x (xx.x)	xx.x (xx.x)		-	-
At day 7	xx.x (xx.x)	xx.x (xx.x)		-	xx.x (xx.x)	xx.x (xx.x)		-	-
In hospital (at least one renal substitution in hospital stay)	xx.x (xx.x)	xx.x (xx.x)	x.xx (x.xx - x.xx)	x.xx	xx.x (xx.x)	xx.x (xx.x)	x.xx (x.xx - x.xx)	x.xx	x.xx
Unknown at 90-day follow up	xx.x (xx.x)	xx.x (xx.x)		-	xx.x (xx.x)	xx.x (xx.x)		-	-
Lost contact for 90-day follow-up	xx.x (xx.x)	xx.x (xx.x)		-	xx.x (xx.x)	xx.x (xx.x)		-	-
Incident renal failure (using KDIGO ≥ 2) at day 3	xx.x (xx.x)	xx.x (xx.x)	x.xx (x.xx - x.xx)	x.xx	xx.x (xx.x)	xx.x (xx.x)	x.xx (x.xx - x.xx)	x.xx	x.xx
KDIGO ≥ 2 or death at day 3	xx.x (xx.x)	xx.x (xx.x)	x.xx (x.xx - x.xx)	x.xx	xx.x (xx.x)	xx.x (xx.x)	x.xx (x.xx - x.xx)	x.xx	x.xx

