Incident renal failure (using KDIGO ≥ 2) at day 7	xx.x (xx.x)	xx.x (xx.x)	x.xx (x.xx - x.xx)	x.xx	xx.x (xx.x)	xx.x (xx.x)	x.xx (x.xx - x.xx)	x.xx	x.xx
KDIGO ≥ 2 or death at day 7	xx.x (xx.x)	xx.x (xx.x)	x.xx (x.xx - x.xx)	x.xx	xx.x (xx.x)	xx.x (xx.x)	x.xx (x.xx - x.xx)	x.xx	x.xx
SOFA > 2 at day 3									
Cardiovascular	xx.x (xx.x)	xx.x (xx.x)	x.xx (x.xx - x.xx)	x.xx	xx.x (xx.x)	xx.x (xx.x)	x.xx (x.xx - x.xx)	x.xx	x.xx
Neurologic	xx.x (xx.x)	xx.x (xx.x)	x.xx (x.xx - x.xx)	x.xx	xx.x (xx.x)	xx.x (xx.x)	x.xx (x.xx - x.xx)	x.xx	x.xx
Coagulation	xx.x (xx.x)	xx.x (xx.x)	x.xx (x.xx - x.xx)	x.xx	xx.x (xx.x)	xx.x (xx.x)	x.xx (x.xx - x.xx)	x.xx	x.xx
Respiratory	xx.x (xx.x)	xx.x (xx.x)	x.xx (x.xx - x.xx)	x.xx	xx.x (xx.x)	xx.x (xx.x)	x.xx (x.xx - x.xx)	x.xx	x.xx
Total SOFA score at day 3	xx [xx - xx]	xx [xx - xx]	x.xx (x.xx - x.xx)	x.xx	xx [xx - xx]	xx [xx - xx]	x.xx (x.xx - x.xx)	x.xx	x.xx
SOFA > 2 at day 7									
Cardiovascular	xx.x (xx.x)	xx.x (xx.x)	x.xx (x.xx - x.xx)	x.xx	xx.x (xx.x)	xx.x (xx.x)	x.xx (x.xx - x.xx)	x.xx	x.xx
Neurologic	xx.x (xx.x)	xx.x (xx.x)	x.xx (x.xx - x.xx)	x.xx	xx.x (xx.x)	xx.x (xx.x)	x.xx (x.xx - x.xx)	x.xx	x.xx
Coagulation	xx.x (xx.x)	xx.x (xx.x)	x.xx (x.xx - x.xx)	x.xx	xx.x (xx.x)	xx.x (xx.x)	x.xx (x.xx - x.xx)	x.xx	x.xx
Respiratory	xx.x (xx.x)	xx.x (xx.x)	x.xx (x.xx - x.xx)	x.xx	xx.x (xx.x)	xx.x (xx.x)	x.xx (x.xx - x.xx)	x.xx	x.xx
Total SOFA score at day 7	xx [xx - xx]	xx [xx - xx]	x.xx (x.xx - x.xx)	x.xx	xx [xx - xx]	xx [xx - xx]	x.xx (x.xx - x.xx)	x.xx	x.xx
Mechanical ventilation-free days within 28 days	xx [xx - xx]	xx [xx - xx]	x.xx (x.xx - x.xx)	x.xx	xx [xx - xx]	xx [xx - xx]	x.xx (x.xx - x.xx)	x.xx	x.xx
Tertiary outcomes	xx.x (xx.x)	xx.x (xx.x)	x.xx (x.xx - x.xx)	x.xx	xx.x (xx.x)	xx.x (xx.x)	x.xx (x.xx - x.xx)	x.xx	x.xx
Death in ICU									
Death in hospital	xx.x (xx.x)	xx.x (xx.x)	x.xx (x.xx - x.xx)	x.xx	xx.x (xx.x)	xx.x (xx.x)	x.xx (x.xx - x.xx)	x.xx	x.xx
Days in ICU (days)	xx.x (xx.x)	xx.x (xx.x)	x.xx (x.xx - x.xx)	x.xx	xx.x (xx.x)	xx.x (xx.x)	x.xx (x.xx - x.xx)	x.xx	x.xx
Days in hospital (days)	xx [xx - xx]	xx [xx - xx]	x.xx (x.xx - x.xx)	x.xx	xx [xx - xx]	xx [xx - xx]	x.xx (x.xx - x.xx)	x.xx	x.xx
Dias no hospital (dias)	xx [xx - xx]	xx [xx - xx]	x.xx (x.xx - x.xx)	x.xx	xx [xx - xx]	xx [xx - xx]	x.xx (x.xx - x.xx)	x.xx	x.xx

95%CI - 95% confidence interval; KDIGO - Kidney Disease Improving Global Outcomes; SOFA - Sequential Organ Failure Assessment; ICU - intensive care unit.

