### Secondary outcomes

The following secondary endpoint analysis were defined:

- Renal replacement therapy up to 90 days.- Acute renal failure incidence defined as Kidney Disease Improving Global Outcomes (KDIGO)^(8)^ stage 2 or 3 evaluated at days 3 and 7. We plan to use both serum creatinine and diuresis for the KDIGO classification. Diuresis was collected on a daily basis during BaSICS, and therefore we will use the average diuresis over 24 hours as the urinary output criteria in KDIGO; creatinine criteria will be used if diuresis information is not registered. In case of a disagreement between creatinine and diuresis criteria for KDIGO, we will consider the worst criteria.- SOFA score assessed both as the total value and as individual components and each of their components separately (Cardiovascular, Neurologic, Coagulation, Hepatic and Respiratory) will be evaluated on day 3 and 7.- Mechanical ventilation-free days within 28 days.

Renal replacement therapy up to 90 days will be estimated using a mixed Poisson model adjusted for age, baseline SOFA and admission type and will be reported as the incidence per 1,000 patient-days. Alternatively, we will also report renal replacement therapy at 90 days in a competing risk model considering death as a competitor for the need for RRT. Incidence of AKI at days 3 and 7 will be tested with mixed generalized linear models with a binomial distribution and the logit link function (also known as a mixed logistic regression model^(9)^) considering site as a random effect; the results will be presented with odds ratios and 95% confidence intervals. Additional analysis combining KDIGO and death will be performed as a supportive analysis to address competitive risks issues.

SOFA score will be tested with a mixed generalized linear model using the distribution that best fits the data (Poisson, gamma, inverse gaussian, or multinomial, among others), and the results will be presented as the mean and/or median differences or ratios with respective 95% confidence intervals using the delta method. Organ dysfunctions at day 3 and 7 (specific SOFA item - cardiovascular, neurologic, coagulation and respiratory as a dichotomous variable defined as higher than 2) will be tested with mixed logistic regression models.

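### The four SOFA > 2 organ items at days 3 and 7 are tested with no stated handling of death, unlike the neighbouring secondary endpoints

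*SAP article*

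**What the plan says.** Under Secondary outcomes, the organ items at days 3 and 7 ("cardiovascular, neurologic, coagulation and respiratory as a dichotomous variable defined as higher than 2) will be tested with mixed logistic regression models"). No covariates, denominator or rule for absent values accompany that sentence. Table 2 has a block for each day (for example "SOFA > 2 at day 7"). Every item there carries an effect measure and a p value for each of the two comparisons, plus an interaction p value, so these are formal secondary results.

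The same section treats death explicitly for the neighbouring endpoints:

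- KDIGO stage 2 or 3: "Additional analysis combining KDIGO and death will be performed as a supportive analysis to address competitive risks issues". Table 2 lists KDIGO-or-death rows at both days.
- Total SOFA: missing after death, then multiply imputed, with a sensitivity analysis that leaves out the study arms.
- Ventilator-free days: a patient who dies within 28 days counts as zero.
- Renal replacement therapy: a competing-risk model beside the Poisson model.

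Under Exploratory analyses, the SAP recognises death as competing with SOFA measurement and plans a Bayesian network for the components with death as an absorbing state. That section is to be reported separately.

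**The concern.** A patient who died on day 2 has no cardiovascular SOFA on day 3 or day 7. Without a rule, that patient drops out of the logistic model, and the comparison is made among those who have a value. Having a value is itself affected by treatment. If one arm prevents early deaths among the sickest, it keeps more patients with organ failure in its denominator and looks worse. If one arm loses more patients with organ failure to death, it looks better.

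Discharge alive from the ICU could act in the same way if organ data stop then. Infusion speed is unblinded, so a difference in discharge timing is conceivable for that comparison. At stake is the reading of eight secondary results (four items, two days) for each factor. The primary analysis is untouched.

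**Working it through.** **The plan's own figure.** "BaSICS was designed to enroll 11,000 patients", "stratified by recruiting site in a 1:1:1:1 ratio", gives 5,500 per arm on each margin. With 35% control mortality and hazard ratio 0.9, treated risk = 1 − 0.65^0.9 = 0.3214 and events = 5,500 × (0.35 + 0.3214) = 3,693. Schoenfeld: |ln 0.9| × √(3,693/4) − 1.96 = 3.20 − 1.96 = 1.24, so power is 89.3%. The SAP says the sample size "allowed for an 89% power to detect a hazard ratio of 0.9 for both interventions", so its figure reproduces. It gives no death or discharge rate at day 3 or 7 and no organ dysfunction rate, so every input below other than 5,500 per arm and the design hazard ratio of 0.9 is an assumption.

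**Moderate illustration.** Assume 30% severe and 70% mild patients (shares w), with organ failure risk f = 50% and 10%, identical in both arms. Control death by day 7 is d = 35% and 5%, that is 0.3 × 0.35 + 0.7 × 0.05 = 14% overall. With q the fraction of survivors who have left measurement, the measured share per stratum is m = w(1 − d)(1 − q), and the observed proportion is P = Σ m f / Σ m. The true odds ratio is 1.00. Rejection is the chance of p < 0.05 in an unadjusted two-proportion test.

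Worked case, day 7, deaths only, early-death hazard ratio 0.9:

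- Control: m = 0.195 and 0.665; P = (0.0975 + 0.0665)/0.860 = 0.1907.
- Treated: d = 1 − 0.65^0.9 = 0.3214 and 1 − 0.95^0.9 = 0.0451; m = 0.2036 and 0.6684; P = 0.1686/0.8720 = 0.1934.
- Odds ratio 1.017, rejection 6% instead of 5%.

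| Scenario | P treated v control | OR | Rejection |
|---|---|---|---|
| Day 7, death HR 0.9 | 0.1934 v 0.1907 | 1.017 | 6% |
| Day 7, death HR 0.8 | 0.1961 v 0.1907 | 1.035 | 10% |
| Day 7, mild discharged 42% v 40% | 0.2298 v 0.2268 | 1.017 | 6% |
| Day 7, mild discharged 45% v 40% | 0.2345 v 0.2268 | 1.044 | 11% |
| Day 7, HR 0.9 and 45% v 40% | 0.2379 v 0.2268 | 1.064 | 18% |
| Day 3, death HR 0.9 | 0.2181 v 0.2169 | 1.007 | 5% |
| Day 3, mild discharged 13% v 10% | 0.2197 v 0.2169 | 1.017 | 6% |

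The day-7 discharge rows also assume 5% of severe survivors discharged in both arms. The day-3 rows assume control deaths of 15% and 2%, 10% of mild survivors discharged unless shown otherwise, and no severe survivors discharged. Discharge rows assume no organ data after ICU discharge.

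**Larger illustration, day 7.** Assume 10% dead and 10% of all randomised with the dysfunction in both arms, and nobody discharged with it.

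- 55% v 50% discharged alive: measured 5,500 × 0.35 = 1,925 and 5,500 × 0.40 = 2,200. 550/1,925 (28.6%) v 550/2,200 (25.0%): OR = (550 × 1,650)/(550 × 1,375) = 1.20. The standard error of ln OR is √(1/550 + 1/1,375 + 1/550 + 1/1,650) = 0.0705, giving 95% CI 1.05 to 1.38, p = 0.0097.
- 53% v 50%: 550/2,035 v 550/2,200: OR 1.11, p about 0.13.
- 50% discharged in both, but one point more of one arm, all with dysfunction, dies: 495/2,145 v 550/2,200: OR 0.90 in favour of the arm with more deaths.

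**What a composite in all randomised patients does.**

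- Moderate case, HR 0.9: treated 0.1280 + 0.1686 = 0.2966; control 0.14 + 0.164 = 0.304; OR 0.97. At HR 0.8 it is 0.93. It follows the mortality difference.
- Only discharge differs (45% v 40%), status of discharged patients known: OR 1.00.
- The same, with discharged patients classed as without the event: treated 0.14 + 0.18525 × 0.5 + 0.36575 × 0.1 = 0.2692; control 0.14 + 0.18525 × 0.5 + 0.399 × 0.1 = 0.2725; OR 0.98. This is the cost of misclassing residual dysfunction.
- Excess-death case above: 11% + 9% v 10% + 10%, so 20% in both and OR 1.00.

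**The case against.** The SAP nowhere states that these models are limited to patients alive and measured. Intention to treat is its default, and restriction is inferred from silence. That is a fair reading of the words, but the default cannot supply a day-7 value for a patient who died on day 4. Without a rule the model runs on those who have one.

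The imputation paragraph speaks of missed SOFA scores at both days in general terms, and the endpoint is defined as total and components, so imputation might extend to the items. But the paragraph opens on the total score and does not say that it reaches the dichotomised items.

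A reader might infer that acute kidney injury shares the defect. On death it does not: the KDIGO-or-death analysis is prespecified and tabulated at days 3 and 7.

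The discharge argument depends on whether organ data continue after the ICU. The document does not say, and data collection rules may sit in the protocol, so that part is conditional only.

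The component Bayesian network shows that the issue was seen, but it is exploratory and reported apart from the secondary results.

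Finally, the composite has its own weakness. In the excess-death example it reads 1.00 while mortality is 11% v 10%. That supports adding it beside the planned models, and does not support replacing them.

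**Conclusion.** The point holds for the four dichotomised SOFA items. They are formal secondary results with no stated handling of death, in a plan that handles it for KDIGO, total SOFA, ventilator-free days and renal replacement therapy. The possible bias is real but of unknown size. It is about 1.01 to 1.06 on the odds ratio scale under moderate assumptions, at most 18% rejection in place of 5%, and close to nil at hazard ratio 0.9 through death alone. It reaches 1.20 only with a 5-point difference in discharge, about half of patients discharged by day 7, and no organ data afterwards. None of those inputs is in the document.

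A reader might infer that these results will be false or have the wrong sign. The document does not support that. Such an outcome needs a between-arm difference in early death or discharge that nobody can state in advance. The illustrations are also unadjusted. If baseline severity entered the model, the bias it carries would shrink, but bias from dysfunction arising after randomisation and leading to death would remain.

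**What to change.** In the Secondary outcomes section and Table 2:

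- Keep the planned mixed logistic models for the four items.
- Add, as a supportive analysis in all randomised patients, SOFA item > 2 or death at day 3 and at day 7, parallel to the KDIGO-or-death rows.
- Where no value exists because the patient left the ICU alive, keep that patient in the denominator of both composites (SOFA item and KDIGO) as without the event. Add one sensitivity analysis using the last observed value.

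The cost is a few sentences and eight table rows (four items, two days). Vital status is needed for the primary outcome and ICU length of stay is a tertiary outcome, so no new data should be required. There are two small downsides. The composite partly repeats mortality, and some patients discharged with residual dysfunction are classed as free of it, which the sensitivity analysis addresses.

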Total SOFA score will be missing if patients died before the measurement time point , and multiple imputation by chain equations using the *mice* R^(10)^ package shall be performed to address the competitive risk bias. Acquired SOFA trend and baseline characteristics will be considered to predict any missed SOFA scores at 3 and 7 days, with the study arms as covariates. Sensitivity analysis without the arms as covariates shall also be performed.

Mechanical ventilation-free days within 28 days will be tested considering the proportion of ventilator-free days in that time frame using zero/one inflated beta or beta-binomial regression assuming zero free-days for those patients who died within that period independently of the amount of time the patient actually used the ventilator. We will consider as ventilation day any day where the patient received any duration of mechanical ventilation. Effect measures shall be presented as the absolute mean difference.

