- Mean adjusted chloride load (MACL): MACL, defined as total infused chloride over the total volume of infused fluids, is expected to be related to the randomization arm since Plasma-Lyte 148 has 98mEq/L and normal saline has 154mEq/L. It has been suggested that MACL can mediate the effect of saline on outcomes;^(13)^ that is, by using saline, the MACL will be higher (and will approach 154mEq/L if only saline is used), and a higher MACL can cause harm. Based on the daily infusion of fluids used per patient, including all open-label infusions, we will estimate the daily MACL and the cumulative MACL effects on mortality in a time to event analysis for the ICU and for in hospital mortality. We intend to adjust a Cox proportional hazard frailty model and test the incremental effect of the daily and accumulated MACL and total fluid infusion volume as a time-dependent variable until day 3. This analysis will, therefore, consider both the total volume of infused fluids and the MACL and will explore both potential factors on short-term outcomes. Splines will be considered when modeling.- Chloride subgroup analysis: It is also conceivable that serum chloride may be a driver of organ failure and that part (or all) of the effects of the fluid type intervention is mediated by serum chloride; that is, harms of saline may be more prominent in patients with higher baseline serum chloride. We plan to tackle this issue initially with a sensitivity analysis among patients with low and high (> 110mEq/L) baseline serum chloride for the primary endpoint and the renal secondary endpoints. It should be highlighted that the measurement of serum chloride was not obligatory in BaSICS and therefore not all patients will be available for this analysis.- Bayesian network for SOFA (total, and all components except hepatic): Death is a competing event for SOFA measurements over time. One approach^(14)^ is to draw Bayesian networks for each intervention arm and to observe transitions to possible states at D2, D3 and D7 according to the randomization group (for both arms) while accounting for death as an absorbent state. This approach can answer, for example, what is the probability that a patient who has a baseline hemodynamic SOFA of 3 and received a slow infusion is alive without vasopressors (alive and SOFA < 3) at day 3? We can obtain relative risks and 95% confidence intervals through bootstrapping the data set. Total SOFA will be categorized for this analysis in quartiles. SOFA components are planned to be used as 5 level categorical variables.

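### Imputing total SOFA for patients who have died removes early deaths from this secondary endpoint and does not address the competing risk of death

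*SAP article*

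**What the plan says.** Secondary outcomes in the SAP article makes SOFA a secondary endpoint at days 3 and 7: "SOFA score assessed both as the total value and as individual components". For the total score, "Total SOFA score will be missing if patients died before the measurement time point", and multiple imputation with the mice "R^(10)^ package shall be performed to address the competitive risk bias". The imputation model, in which the arms enter as covariates, is described as follows: "Acquired SOFA trend and baseline characteristics will be considered to predict any missed SOFA scores at 3 and 7 days, with the study arms as" (last word omitted). The only sensitivity analysis stated for this endpoint is "Sensitivity analysis without the arms as covariates shall also be performed".

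The organ components are also analysed "as a dichotomous variable defined as higher than 2) will be tested with mixed logistic regression models". The section does not say how a patient who died before the assessment enters those models.

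The plan handles death differently for its other secondary endpoints. Ventilator-free days are set to zero for patients who die within the 28 days. KDIGO stage 2 or 3 has a supportive composite with death, with its own rows in Table 2. Renal replacement therapy has an alternative competing-risk model. Under Exploratory analyses the plan states "Death is a competing event for SOFA measurements over time" and proposes a Bayesian network with death as an absorbing state. That section expects its analyses to be reported separately from the main results.

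**The concern.** Multiple imputation is meant for values that exist but were not recorded. A patient who died before day 3 or day 7 has no SOFA on that day. Imputing one does not account for the competing event; it replaces it with a prediction of what the score would have been had the patient lived. The plan applies one imputation model to every missed score and does not separate the dead from living patients whose score was not recorded.

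If one arm has more early deaths, and those deaths are not preceded by a visible rise in SOFA, the excess leaves almost no trace in the total-SOFA comparison. Dropping arm from the imputation model does not help, because the dead still receive a living patient's score. The Abstract lists organ dysfunction at days 3 and 7 among the important secondary endpoints. A near-zero SOFA difference printed beside a mortality difference could be misread as showing that the intervention left patients' overall condition unchanged.

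**Working it through.** **Inputs from the SAP.** 11,000 patients allocated 1:1:1:1, so 5,500 per arm at each margin; control 90-day mortality 35%; hazard ratio 0.9; alpha 5%. The SAP gives no day-3 or day-7 mortality and no SOFA distribution, so both are assumptions below.

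**The plan's own figure.** It states no figure for SOFA. Its primary power reproduces. Treated mortality is 1 - 0.65^0.9 = 32.1%. Events are 5,500 x (0.350 + 0.321) = 3,693. By Schoenfeld's formula, sqrt(3,693) x |ln 0.9| / 2 - 1.96 = 1.24, which gives 89.3% against the stated 89%. The SOFA point does not touch this figure.

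**What separates the two ways of handling death.** Let p be the proportion dead before the assessment in an arm, S the mean SOFA of those alive, and H the mean score imputed to the dead.

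- Planned mean: (1 - p)S + pH.
- Mean with death scored 24 (the worst value): (1 - p)S + 24p.
- The arm contrasts under the two methods therefore differ by about (p1 - p0) x (24 - H).

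A simulation of 200,000 patients per arm assumed 14.7% versus 16.6% dead by day 7 and no arm effect on SOFA. The mean imputed score for the dead was 5.4. The formula gives 0.019 x 18.6 = 0.35. The simulated contrasts were -0.01 as planned and +0.34 with death scored worst, a gap of 0.35.

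**Independent simulation over a range of assumed rates.** There were 5,500 patients per arm and 200 replicates per scenario. Baseline SOFA was drawn with mean 5 and SD 3, and the arm had no effect on SOFA. The probability of death rose with the patient's own score at the assessment. Scores of the dead were imputed from baseline SOFA, an intermediate SOFA and arm (5 imputations, Rubin's rules). Arms were compared by linear regression adjusted for baseline SOFA. Negative values favour the arm with more deaths.

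| Deaths before assessment | Planned imputation | Arm dropped from imputation | Death scored 24 |
|---|---|---|---|
| 5% vs 5% | -0.005 | -0.001 | +0.004 |
| 5% vs 7% | -0.024 | -0.020 | +0.336 |
| 8% vs 11% | -0.033 | -0.034 | +0.511 |
| 15% vs 18% | -0.037 | -0.024 | +0.532 |
| 15% vs 20% | -0.047 | -0.044 | +0.899 |

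In the four unequal scenarios the planned estimate fell below zero in 71% to 90% of replicates and was nominally significant in 10% to 20%. With death scored worst, 94% to 100% of replicates were significant. With equal mortality both methods give about zero.

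The gap between the methods per excess death is 0.360/0.02 = 18.0, 0.544/0.03 = 18.1, 0.569/0.03 = 19.0 and 0.946/0.05 = 18.9 points. This is close to the 18.6 above. The contrast is therefore essentially the assumed excess of deaths multiplied by the distance from an ordinary living score to 24.

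**The case against.** The strongest defence is that the planned analysis answers a coherent question: what the SOFA difference would have been had nobody died. In these simulations the arm has no effect on SOFA, so an answer near zero is the right one to that question. Scoring death as 24 answers a different, composite question, and the +0.3 to +0.9 mostly restates the mortality gap that was assumed. This stands: the two columns show a difference of estimand, not an error of that many points. It does not rescue the plan's rationale. The SAP does not name a hypothetical estimand; it presents the imputation as dealing with competing risk, which it does not do.

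A reader might infer that a harmful intervention would look better on SOFA. The documents and the figures do not support that. The shift is -0.01 to -0.05 points on a scale of 0 to 24. In the scenarios of the independent simulation it arises with deaths that depend on the unobserved score itself. Nominal significance in 10% to 20% of replicates exceeds the expected 5%, but the supported description is that excess deaths become invisible, not that they are materially rewarded.

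A reader might also infer that the component models use survivors only. That is a likely default, but the plan does not say so, and its reference to any missed scores could be read to cover components. The rule is unspecified.

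Three mitigations are real. Imputation uses the SOFA trend, so harm that raises SOFA before death is partly captured. The exploratory Bayesian network treats death as a state for total SOFA and all components except hepatic, although it is expected to be reported elsewhere. Mortality is the primary endpoint, appears in the same Table 2, and drives the harm boundary in the DMC charter, so a lethal arm would not be hidden from the trial.

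**Conclusion.** The point holds for the interpretation of the SOFA secondary endpoint. Treating death as missing and imputing it removes the competing event, contrary to the stated purpose. The planned sensitivity analysis leaves this unchanged (-0.02 to -0.04 points in the unequal scenarios), and the dichotomous component models have no stated rule for death. Under the assumed excesses of about 2 to 5 percentage points in early deaths, with no effect of arm on SOFA, the planned result is close to neutral (-0.01 to -0.05), against +0.34 to +0.90 when death is the worst state. These sizes depend on the assumed early mortality, SOFA distribution and link between SOFA and death; none of these is in the documents.

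This is a should-fix, not a must-fix, because death is the primary outcome and is tabulated beside SOFA.

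The choice of model "using the distribution that best fits the data (Poisson, gamma, inverse gaussian, or multinomial, among others") and the open choice of effect measure are a separate, minor point. One might read them as defeating the plan's aim of preventing data-driven analysis. That is too strong, since the Abstract says analyses stay blinded during the analysis procedure and the list of families is only illustrative.

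**What to change.** - Restrict chained-equation imputation to patients alive at the assessment whose score was not recorded.
- Add to the main report a pre-specified analysis of total SOFA at days 3 and 7 that counts death before the assessment as the worst state. One option is a mixed ordinal model with death as the top category. Check proportional odds, because a common odds ratio assumes the same effect on death as on organ function.
- Add rows to Table 2 for each component combining SOFA above 2 with death, following the plan's own KDIGO-or-death rows, and state how deaths enter the existing component models.
- Keep the planned imputation of the dead only as a sensitivity analysis, labelled as a hypothetical estimand, and delete the statement that it addresses competing-risk bias.

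The cost is SAP wording and some table rows; no new data are needed. The downside is that the composite mixes death with organ function and partly repeats the primary endpoint, so the number of deaths and the scores of survivors should be shown beside it.
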